### Participant recruitment and data collection

The study will follow a fixed study design (Additional file 1). Sample size is determined based on a previous study where a mean difference of BMI was found 1.48 between intervention and non-intervention adolescent groups after 3-months of motivational interview [23]. Expecting a similar difference, calculated sample size is 274 in each group considering effect size (E) = 1.48; standard deviation (S) = 5.98; standardized effect size (E/S) = .25; significance level, α (two-sided) = 0.05; β = 1- power = 0.2, non-response rate = 5%]. A complete list of grade-ten students will be prepared after collecting their class roll and batch number from the administrative offices of the selected schools. All the students of grade-ten will be invited to participate in the study through announcement and personal contact prior to the date of data collection.

At first, a baseline survey will be conducted among the grade ten students of both schools by a pre-tested questionnaire to attain their current status of knowledge, attitude and practices related to NCDs. Then, students from the intervention school who reported at least two NCDs risk behaviors will be invited to participate in a health education session through phone call to their parents. Selected students who will present at the day of intervention will be considered having implied consent from their parents and will be enrolled in the intervention group up to the attainment of the required sample size. Enrolled students will be given intervention through health education session. Students with any kind of physical disability or limited movement will be excluded from the study. Students from the control group will receive a one-hour session on carrier guidance. Students will be kept blind about the intervention they received. After 3 months of the baseline survey, a post-intervention survey will be conducted among the participants from both intervention and control group using the same questionnaire.

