### Practice

Practice questions will be used to evaluate dietary habit, physical activity, smoking, alcohol and substance abuse.

Based on WHO recommendations and standard practices for adolescent age, the following practices will be measured in this study.Dietary habit: presence of at least two of the following four habits will be accounted as having dietary risk behaviori.*Inadequate fruit consumption:* Less than five servings of fruits per dayii.*Inadequate vegetable consumption:* Less than five servings of vegetables per dayiii.*Excessive salt consumption:* Taking extra or raw salt during every mealiv.*Sugar Sweetened Beverage (SSB) consumption:* Consuming SSB more than 3 days per weekPhysical activity*:* Not meeting 60 min physical activity of moderate intensity per day will be regarded as physically inactive.Smoking and alcohol: Smoking regularly in the last 30 days or exposing to passive smoking more than 3 days per week will be accounted as in risk of smoking. Any amount of alcohol intake or any substance abuse in the last 30 days will be regarded as at risk.

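### The smoking outcome counts active smoking only when it is regular, with no cut-off given, and merges it with passive exposure, so starting to smoke is largely masked

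*Protocol article*

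**What the plan says.** The Practice section of the protocol article defines the binary practice outcomes. For tobacco, the rule reads, up to its last word, which names the smoking risk: "Smoking regularly in the last 30 days or exposing to passive smoking more than 3 days per week will be accounted as in risk of". The active part is "Smoking regularly in the last 30 days", with no count of days or cigarettes. The passive part is "exposing to passive smoking more than 3 days per week". The two are joined by an or. The next sentence treats alcohol and substances differently: "Any amount of alcohol intake or any substance abuse in the last 30 days will be regarded as at risk". The section introduces all of its definitions as "Based on WHO recommendations and standard practices for adolescent age" and gives no reason for the different thresholds.

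Other sections bear on this rule:

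- **The intervention, Issue 4.** The session covers why adolescents start smoking. It then turns to avoiding starting, quitting and reducing passive smoking.
- **Participant recruitment and data collection.** Entry uses a count of risk behaviours: "students from the intervention school who reported at least two NCDs risk behaviors will be invited to participate in a health education session". On timing, "After 3 months of the baseline survey, a post-intervention survey will be conducted".
- **Statistical analysis plan.** Before-after data are analysed with paired t-tests and McNemar's test. The two groups are also compared on practices before and after the intervention.

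The article sets no separate outcome for any active smoking or for starting to smoke.

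**The concern.** The rule decides which changes in smoking the trial can record. McNemar's test uses only students whose code changes between the two surveys, so a change in behaviour that leaves the code as it was contributes nothing.

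Two features work against recording a new smoker. First, only regular smoking counts, and after three months some starters may still smoke only occasionally. Second, a student already coded at risk through second-hand exposure has no further code to move to. In the other direction, cutting down to occasional smoking and stopping altogether can produce the same change of code.

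At stake is the meaning of the smoking result. A null finding could arise although fewer intervention students started smoking. An apparent improvement could reflect less second-hand exposure, cutting down or quitting, and the indicator could not say which.

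**Working it through.** **The plan's own figure.** The only sample size in the article is 274 per group, based on BMI. With E = 1.48, S = 5.98, two-sided alpha 0.05 and 80% power, n = 2(1.96 + 0.842)² × (5.98/1.48)² ≈ 257. With 5% non-response, 257/0.95 ≈ 271, within about 1% of 274. It says nothing about smoking, and the article gives no smoking rate. The main check is therefore one of definitions.

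**Transitions under the stated rule.** Exposed means passive exposure on more than 3 days per week. Occasional means any smoking that falls short of regular, wherever that line lies.

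| Student | Baseline code | End-line code | Change recorded |
|---|---|---|---|
| Not exposed, starts, occasional | 0 | 0 | none |
| Not exposed, starts, regular | 0 | 1 | yes |
| Exposed throughout, starts at any level | 1 | 1 | none |
| Not exposed, regular to occasional | 1 | 0 | same as quitting |
| Not exposed, regular to none | 1 | 0 | yes |
| Exposed throughout, regular to none | 1 | 1 | none |
| Never smokes, exposure falls to 3 days or fewer | 1 | 0 | same as quitting |

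Of the three ways of starting, one is recorded. Replacing regular by any smoking repairs the first row and separates the fourth from the fifth. The third and sixth rows stay as they are, and the seventh is still indistinguishable from quitting, because the two components remain merged.

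**Share of starters recorded (illustration, assumed rates).** Let e be the share exposed, unchanged over follow-up, and r the share of starters who smoke regularly by 3 months, independent of e. The share of starters whose code changes is (1 − e) × r.

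- Lowest: e = 0.6, r = 0.1 gives 0.4 × 0.1 = 4%.
- Highest: e = 0.2, r = 0.5 gives 0.8 × 0.5 = 40%.
- With any smoking counted but the components still merged, the share is 1 − e, or 40% to 80%.
- With active smoking as its own indicator, it is 100%.

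**Effect on a comparison of the groups at end line (illustration).** Assume no active smokers at baseline, 10% of control and 4% of intervention students starting, 274 × 0.95 ≈ 260 per group, and clustering ignored. The end-line proportions are p = e + (1 − e) × i × r, where i is the share starting. Power is Φ[(d − 1.96·SE0)/SE1], where d is the difference, SE0 the pooled and SE1 the unpooled standard error.

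| Definition | Control | Intervention | Power |
|---|---|---|---|
| Any active smoking, own indicator | 10.0% | 4.0% | 77% |
| Regular smoking only, own indicator (r = 0.25) | 2.5% | 1.0% | 26% |
| Any smoking, merged with exposure (e = 0.4) | 46.0% | 42.4% | 13% |
| Stated rule (r = 0.25, e = 0.4) | 41.5% | 40.6% | 4% |

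For the first row, d = 0.06, SE0 = 0.0224 and SE1 = 0.0222, so Φ(0.73) = 77%. For the last row, d = 0.009 and both standard errors are 0.0431, so Φ(−1.75) = 4%.

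The two merged rows compare everyone at end line. An analysis confined to students not exposed at baseline would lose less. With 260 × 0.6 = 156 per group:

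- Any smoking (10% v 4%): d = 0.06, SE0 = 0.0289, SE1 = 0.0287, so Φ(0.12) ≈ 55%.
- Regular smoking only (2.5% v 1.0%): d = 0.015, both standard errors 0.0148, so Φ(−0.95) ≈ 17%.

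The ranking of definitions therefore does not depend on the whole-group comparison, but the very low figures do.

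**The case against.** The strongest reply is that the rule is a deliberate choice. Reducing passive smoking is itself a topic of the session, so counting frequent exposure serves a stated aim. The general objective is to reduce behavioural risk factors, and no section names initiation or cessation as an endpoint. The definitions are attributed to outside recommendations that the reader cannot see here, and the questionnaire (Additional file 2) may define regular smoking or record any smoking.

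Part of this stands. Passive exposure belongs among the outcomes, and different cut-offs for tobacco and alcohol are not an error in themselves. A student who smokes every weekend might count as regular, so that example cannot be used with confidence. None of it answers the merging of two components that can move independently. If the questionnaire does record any smoking, the stated outcome rule still discards that information.

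A reader might also infer more than the text supports:

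- **That all occasional smokers and starters are coded not at risk.** Those exposed on more than 3 days per week are coded at risk through the or.
- **That any second-hand exposure counts, as any alcohol does.** Passive exposure has its own threshold.
- **That starting to smoke cannot be seen.** A starter who becomes regular and was not already exposed does change code.
- **That many smokers are kept out of the intervention.** The rule does feed the entry count, but the effect is probably small. Dietary risk needs two of four habits, and eating under five servings of fruit and under five of vegetables are two of them. The Background describes low intake of both as common, so an inactive student will usually reach two risks without smoking.
- **That a definite number is misclassified.** If 5–15% of 274 students smoke and half do so occasionally, that gives 7–21 students. Removing the 20–60% captured through exposure leaves 274 × 0.05 × 0.5 × 0.4 ≈ 3 to 274 × 0.15 × 0.5 × 0.8 ≈ 16. Every rate here is assumed.

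**Conclusion.** The point holds as a weakness of a stated outcome definition. Regular smoking has no cut-off, is on its face a stricter test than the any-amount rule for alcohol, and is merged with passive exposure. Occasional smokers and new starters without frequent exposure are coded not at risk, cutting down can score as quitting, and starting among exposed students leaves no trace. A change that the session targets is therefore largely masked, not invisible.

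The direction follows from the text alone. The size does not: the 4–40% of starters recorded and the power figures rest on assumed exposure, initiation and regular-smoking rates, on independence between exposure and smoking, and on ignoring clustering by school. The BMI-based sample size is unaffected. Smoking is one of several practice outcomes, but it is a named target behaviour, so the definition should be corrected.

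**What to change.** Make two changes to the Practice section, together:

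1. Define active-smoking risk as any smoking in the last 30 days, in line with the alcohol rule beside it.
2. Analyse active smoking and passive exposure as two separate indicators at baseline and end line, and keep frequency (regular or occasional, with the cut-off stated in days) as a descriptive item.

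The first change alone is not enough: in the illustration it raises power in the whole-group comparison from about 4% to 13%, against 77% for active smoking on its own. The protocol should also say whether the two indicators count as one risk behaviour or two for the entry rule.

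The cost is a few lines of wording and a recode if the questionnaire already asks about any smoking and exposure separately. If it does not, an item must be added before the baseline survey. The downsides are that some experimental smokers will count as at risk and that there is one more practice indicator to report.

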### Physical measurement

#### Blood pressure

Blood pressure will be measured by an automatic digital sphygmomanometer (HEM-8712, Omron, Kyoto, Japan). Students will be asked to sit down on a chair and rest their right elbow on a table. Blood pressure will be measured three times allowing at least 5 min interval between each measurement. The mean of second and third measurement will be taken into analysis. Presence of systolic blood pressure ≥ 130 mm of Hg and/or diastolic blood pressure ≥ 80 mm of Hg will be considered as having high blood pressure.

#### Height

Height will be measured by a portable and non-stretchable measuring tape. Students will be asked to remove their shoes and head gear, if any and stand straight on the flat floor against a wall, facing the interviewer. Their heels will be in touch of the wall. Interviewers will make sure that their eyes will be at the same level as the ear. Height will be recorded in centimeter to the nearest millimeter.

#### Weight

Weight will be measured by portable digital weighing machine (Medisana Bathroom Glass Scales). The machine will be placed on a flat floor. Students will be asked to remove their shoes and extra cloths, if any, and stand straight on the machine hanging their arms by their sides. Weight will be recorded in kg.

#### Body mass index (BMI)

The ratio of body weight in kilogram and the height in meter square will be considered as BMI. Classification of BMI will be done as following-.

Underweight (Less than 18.5); Normal weight (18.5–24.9); Overweight (25.0–29.9) and Obese (More than 30.0).

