## Objectives

### General objective

To design and investigate the efficacy of a health education intervention to reduce NCD related behavioral risk factors among adolescents in institutional settings of Bangladesh.

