### Ethical consideration

This study protocol got ethical clearance from Institutional Review Board (IRB) of BSMMU (BSMMU/2018/5958). Written permission will be obtained from the authorities of both schools and informed written assent will be collected from every participant prior to participation. Parents or legal guardians of the selected students will be informed about the intervention over telephone and through notice on school diary. If the parents send their children on the day of intervention, it will be regarded as their implied consent [28] to let their children participate in the health education intervention. No written consent will be obtained from the guardians other than the implied consent which has been approved by the IRB, BSMMU.

All the physical measurement will be taken in a separate room maintaining privacy and confidentiality. Female volunteer medical students will measure blood pressure and anthropometric measurements of the female participants.

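### One fixed adult-type set of BMI cut-offs for grade-ten boys and girls will tend to overstate underweight and understate overweight and obesity in the descriptive classes

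*Protocol article*

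**What the plan says.** The section on body mass index defines the measure without reference to age or sex: "The ratio of body weight in kilogram and the height in meter square will be considered as BMI". It then fixes the classes: "Underweight (Less than 18.5); Normal weight (18.5–24.9); Overweight (25.0–29.9) and Obese (More than 30.0". It names no percentile, z-score or growth reference, and no other section of the article qualifies this rule.

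The people classified are school pupils. Under participant recruitment, "All the students of grade-ten will be invited to participate in the study", and the general objective is "to reduce NCD related behavioral risk factors among adolescents in institutional settings of Bangladesh". Both sexes take part: the ethics section provides that "Female volunteer medical students will measure blood pressure and anthropometric measurements of the female participants". Ages are not stated.

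**The concern.** In people who are still growing, a given BMI does not mark the same weight status at every age and in both sexes. A single adult-type list therefore puts some pupils in the wrong class. Where age-appropriate limits are lower than the adult ones, the errors run one way at each end: some pupils of normal weight are called underweight, and some overweight pupils are called normal.

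At stake are the reported shares of underweight, overweight and obese pupils, and which pupils are counted as crossing a class limit between the two surveys. The article fixes this rule itself, so it is not a detail left to a separate analysis plan.

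There is also a drafting slip. The overweight class ends at 29.9 and the obese class starts above 30.0, so a BMI of exactly 30.0 belongs to no class.

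**Working it through.** **Step 1. Does the sample size depend on the classes?**

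Inputs from the section on participant recruitment and data collection: mean BMI difference 1.48, SD 5.98, two-sided α 0.05, power 0.80, non-response 5%.

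- n per group = 2 × (1.960 + 0.842)² × (5.98 / 1.48)² = 256.3, rounded up to 257.
- Allowing for non-response: 257 / 0.95 = 270.5, rounded up to 271.

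The stated 274 is within 3% of this. The calculation uses BMI as a continuous mean and contains no cut-off, so changing the class limits leaves it as it is.

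**Step 2. Does enrolment depend on the classes?**

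Pupils of the intervention school are enrolled if they report at least two risk behaviours. The behaviours defined under Practice are diet, physical activity, smoking, and alcohol or substance use. BMI class is not among them, so enrolment is unaffected.

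**Step 3. How far could the reported shares be out?**

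From the article: the limits 18.5 and 25.0. Assumed, because the article gives none: a log-normal BMI distribution, its mean m and SD s, and age-appropriate limits lower than the adult ones by k = 0.5 to 2 kg/m². The SD of 5.98 in the last row of the second table is the article's own planning value; the means and other SDs are assumptions.

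Formulas:

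- σ² = ln(1 + (s/m)²) and μ = ln(m) − σ²/2
- underweight share = Φ((ln(18.5 − k) − μ)/σ)
- overweight or obese share = 1 − Φ((ln(25 − k) − μ)/σ)
- k = 0 gives the protocol's rule

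For m = 20 and s = 3, μ = 2.9846 and σ = 0.1492. At k = 0 the standardised limits are −0.448 and 1.571, giving 32.7% underweight and 5.8% overweight or obese. At k = 2 they are −1.215 and 1.012, giving 11.2% and 15.6%.

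| k (kg/m²) | Underweight | Overstated by (points) | Overweight or obese | Understated by (points) |
|---|---|---|---|---|
| 0 (protocol) | 32.7% | – | 5.8% | – |
| 0.5 | 26.4% | 6.3 | 7.6% | 1.8 |
| 1 | 20.6% | 12.1 | 9.7% | 3.9 |
| 1.5 | 15.5% | 17.2 | 12.4% | 6.6 |
| 2 | 11.2% | 21.5 | 15.6% | 9.8 |

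Other assumed distributions, over the same range of k:

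| Mean, SD | Underweight: protocol rule, then lower limits | Overweight or obese: protocol rule, then lower limits |
|---|---|---|
| 20, 4 | 38.4%, then 33.3% to 19.2% | 11.0%, then 13.1% to 21.0% |
| 21, 4 | 28.2%, then 23.5% to 11.8% | 15.4%, then 18.1% to 28.2% |
| 22, 5.98 | 30.3%, then 26.8% to 17.3% | 27.0%, then 29.6% to 38.2% |

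The direction is the same in every row, as it must be once the limits are lowered. The size varies about fivefold with k, which the article does not let us fix.

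**The case against.** The strongest reply is that the classes are peripheral. The statistical analysis plan section names knowledge, attitude and practice for the between-group comparison and for the regressions on socio-demographic variables. It names no test of BMI class. The same limits apply in both schools and at both surveys, only 3 months apart, so the cut-offs alone do not bias a comparison between schools or over time. Pupils near adult age would be affected little or not at all. All of this stands, and it limits the point to descriptive labelling.

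Several stronger readings are tempting but not supported:

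- **That any before-after change in class would be wrong.** The rule is constant across surveys. What changes is which limit a pupil is counted as crossing, not the fairness of the comparison.
- **That the article contradicts itself.** The Practice section opens with "Based on WHO recommendations and standard practices for adolescent age, the following practices will be measured in this study". That sentence is about practices and makes no promise about BMI.
- **That values between 24.9 and 25.0 are lost.** This is ordinary one-decimal notation. Only exactly 30.0 is unassigned.
- **That one large figure can be quoted.** Fixing the limits at, say, 16.5 and 23 takes k = 2, the top of the range. The limits drive the result and have to be varied.
- **That obesity as a session topic makes the classes central to the analysis.** That is teaching content, not an analysis.

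**Conclusion.** The point holds in a limited form. Following the stated rule would tend to overstate underweight and understate overweight or obesity among the pupils. With mean 20, SD 3 and limits 0.5 to 2 kg/m² below the adult ones, the errors are about 6 to 21 percentage points and about 2 to 10 points respectively.

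These sizes rest on the assumed distribution and limits. The direction rests only on age-appropriate limits lying below the adult ones. The true size cannot be derived from the article. The between-school comparison, mean BMI, the sample size and enrolment are not biased. The matter is worth correcting because the reported weight status would mislead and the correction is cheap, but it does not threaten the main comparison.

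**What to change.** - In the section on body mass index, name one age- and sex-specific BMI-for-age reference and derive the weight-status classes from it.
- State the boundaries as closed at one end, so that every value falls in exactly one class.
- Keep mean BMI in kg/m² as the continuous measure, because the sample size was set on that scale (1.48, SD 5.98). Report the BMI-for-age z-score alongside it, not in its place.

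The cost is some recoding. It also needs age or date of birth, as well as sex, for each pupil. The analysis section lists gender among its socio-demographic examples but not age, and the questionnaire is in a supplementary file not shown here, so the sponsor should confirm that age or date of birth is recorded in its socio-demographic section.

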#### Waist and hip circumference

Waist and hip circumference will be measured by a stretch-resistant measuring tape and recorded in centimeter to the nearest millimeter. Waist circumference will be measured at the midpoint between the lower margin of the last rib and the iliac crest and hip circumference will be measured at the widest part of the buttock with the tape parallel to the floor following WHO guideline [27]. For both the measurements, students will be asked to stand straight with feet close together and arms at the side. The measurement will be taken at the end of normal expiration.

